### 6.2 Transformations to be applied

In order that the sum of Allogenic Blood Products and its constituents adequately represent the exposure to donors the following transformations will be applied before any derivations:

Platelets:

1 apheresis unit = 4 allogeneic units,  
1 non-apheresis unit = 4 allogeneic units

Frozen Plasma (used in transfusions):

1 apheresis unit = 2 allogeneic units,  
1 non-apheresis unit = 1 allogeneic unit

Transfusion units without any information about apheresis are handled as apheresis units.

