#### **7.2.3 Bleeding Data**

The comparison of 'major' bleeding based on the validated e-CABG and universal definition of perioperative bleeding (UDPB) in cardiac surgery (1, 72) (Table 4) will be assessed. The UDPB is a multistage definition for perioperative bleeding based on easily measured clinical end points, including total blood loss from chest tubes within 12 hours, allogeneic blood products transfused, surgical re-exploration including cardiac tamponade, delayed sternal closure, and the need for salvage treatment.

Depending on these components, bleeding is graded as insignificant, mild, moderate, severe, or massive. (Table 4) (72).

**Table 4 Bleeding categories according to the UDPB in adult cardiac surgery (if different categories indicate mixed definitions of bleeding, the worst definition applies) (72)**

| Bleeding definition     | Postoperative chest tube blood loss within 12 h (mL) | RBC (units) | FP (units) | PLT (units) | Cryoprecipitate | PCCs | rFVIIa | Reexploration /tamponade |
|-------------------------|------------------------------------------------------|-------------|------------|-------------|-----------------|------|--------|--------------------------|
| Class 0 (insignificant) | <600                                                 | 0           | 0          | 0           | No              | No   | No     | No                       |
| Class 1 (mild)          | 601–800                                              | 1           | 0          | 0           | No              | No   | No     | No                       |
| Class 2 (moderate)      | 801–1000                                             | 2–4         | 2–4        | Yes         | Yes             | Yes  | No     | No                       |
| Class 3 (severe)        | 1001–2000                                            | 5–10        | 5–10       | N/A         | N/A             | N/A  | No     | Yes                      |
| Class 4 (massive)       | >2000                                                | >10         | >10        | N/A         | N/A             | N/A  | Yes    | N/A                      |

FP, frozen plasma; N/A, not applicable; PCC, prothrombin complex concentrate; PLT, platelets; rFVIIa, recombinant activated factor VII; UDPB, universal definition of perioperative bleeding.

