### 3.5 Per-Protocol (PP) Population

The Per-Protocol (PP) Population will include all patients of the IIT population, excluding patients with important protocol deviations that may affect the statistical analysis. The following patients will be excluded by default:

- Patients who receive an IMP different to the IMP assigned by randomization
- Patients who receive less than 80% of the planned dose
- Patients who significantly violate inclusion/exclusion criteria

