#### 4.6 Efficacy

The primary population for the analysis of the efficacy of the IMPs will be the ITT. The primary efficacy endpoints will also be analyzed for the PP population.

The analysis of efficacy will focus on the following primary endpoints:

P1. Treatment response, defined as effective if no additional hemostatic intervention (such as administration of hemostatic agents including a second dose of IMP, platelet transfusion, or surgical re-exploration) in the time windows

- from 60 minutes to 4 and 24 hours after initiation of the first dose of IMP,
- *from initiation of the first dose of IMP to 4 and 24 hours.*

Otherwise, treatment response will be considered as not effective, see section 6.1. If the dose of IMP is repeated within less than 60 minutes, treatment response to the IMP will be assessed for the time frames after the second IMP dose only.

P2. Amount of allogeneic blood products (for each type of product and cumulatively) administered

- during the first 24 hours after the start of surgery,
- *during the first 24 hours after the end of CPB,*
- *during the first 24 hours after randomization,*
- *during the first 24 hours after the start of first IMP dose.*

P3. Number of patients who do not receive any allogeneic blood product (in total and for each type separately)

- during the first 24 hours after the start of surgery,
- *during the first 24 hours after the end of CPB,*
- *during the first 24 hours after randomization,*
- *during the first 24 hours after the start of first IMP dose.*

In addition the following efficacy endpoints will be explored:

S1. Number of partial or full IMP doses of PCC and FP administered

- during the first 24 hours after the start of surgery.
- *during the first 24 hours after the end of CPB,*
- *during the first 24 hours after randomization,*
- *during the first 24 hours after the start of first IMP dose.*

|                           |                 |             |               |
|---------------------------|-----------------|-------------|---------------|
| Statistical Analysis Plan | Version 2.0     |             | Page 13 of 19 |
| Sponsor                   | [name] | Protocol No | FARES         |

S2. Incidence of major bleeding, using the universal definition of perioperative bleeding (UDPB) in cardiac surgery scores and their individual components

- during the first 24 hours after start of surgery,
- *during the first 24 hours after the end of CPB,*

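### SAP 6.2 sets no limit on its donor-exposure conversion; read literally, it can raise the unmodified UDPB grade of patients given apheresis or unlabelled plasma

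*Combined protocol and SAP*

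**What the plan says.** SAP 6.2 opens with a purpose, "In order that the sum of Allogenic Blood Products and its constituents adequately represent the exposure to donors", and then gives the timing: "the following transformations will be applied before any derivations". For plasma the factors are "1 apheresis unit = 2 allogeneic units" and "1 non-apheresis unit = 1 allogeneic unit". It adds a default: "Transfusion units without any information about apheresis are handled as apheresis units".

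SAP 6.1 lists four derived variables: response at 4 h, response at 24 h, ABP and ABPadj. Plasma is a component of ABP. UDPB is not listed, so the SAP gives no derivation for it.

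UDPB is nevertheless analysed. SAP 4.6 has "S2. Incidence of major bleeding, using the universal definition of perioperative bleeding (UDPB) in cardiac surgery scores and their individual components", together with a modified version that leaves out PCC and FP. The grading rule is Table 4 of protocol 7.2.3. Its FP column is in units: 2–4 is class 2 (moderate), 5–10 is class 3 (severe) and more than 10 is class 4 (massive). Any PCC use is class 2. Across components, "if different categories indicate mixed definitions of bleeding, the worst definition applies".

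**The concern.** The conversion yields donor exposures, whereas Table 4 is cut on units transfused. If the conversion is run upstream of everything, as the timing clause says, the FP column is read on the wrong scale for apheresis and unlabelled plasma. Because the worst component sets the class, no other component can bring an inflated plasma grade back down.

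The error would not be balanced between arms. Assigned treatment in one arm is plasma, which is counted and can be doubled. In the other it is PCC, which Table 4 grades only as used or not used. S2 could therefore show more severe bleeding with FP partly because of how units were counted. This matters in a pilot whose purpose is to help choose the Phase 3 primary endpoint.

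**Working it through.** The plan states no figure for this point, so there is nothing to reproduce. The check maps protocol doses through Table 4 with and without conversion.

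**Inputs**
- One FP dose: 3 U (IBW ≤60 kg) or 4 U (IBW >60 kg), protocol 5.1.2.
- Plasma factors: ×2 for apheresis or unlabelled, ×1 for non-apheresis, SAP 6.2.
- FP cut-points and the PCC grade: protocol Table 4.
- FP for both arms from the third order on: protocol 3.2 and SAP 1.2.

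**Formula.** Let n be units transfused and k the number that are apheresis or unlabelled. Converted units = 2k + (n − k) = n + k.

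**Single dose**

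| Dose | k | Converted units | Class as transfused | Class after conversion |
|---|---|---|---|---|
| 3 U | 0 | 3 | 2 | 2 |
| 3 U | 1 | 4 | 2 | 2 |
| 3 U | 2 | 5 | 2 | 3 |
| 3 U | 3 | 6 | 2 | 3 |
| 4 U | 0 | 4 | 2 | 2 |
| 4 U | 1 | 5 | 2 | 3 |
| 4 U | 4 | 8 | 2 | 3 |

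The grade changes once k ≥ 2 in a 3 U dose or k ≥ 1 in a 4 U dose.

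**Two doses.** As transfused, 6 U and 8 U are both class 3. Fully converted they are 12 and 16, both class 4. Class 4 needs n + k > 10, so k ≥ 5 of 6 units or k ≥ 3 of 8.

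**PCC arm.** One or two PCC doses are class 2 from the product alone, with or without conversion. If such a patient later receives 3 U of FP, all apheresis or unlabelled, the count becomes 6 and the class moves from 2 to 3.

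**Other columns.** Red cells have no conversion factor. Platelets in Table 4 are graded by use and not by count, so the platelet factor cannot change a class. The modified UDPB omits FP and PCC, so the plasma factor cannot reach it.

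**How often a single dose would cross.** The documents give no apheresis or unlabelled share. Assume each unit has that status independently with probability q. Then P(class 3) is 3q²(1 − q) + q³ for a 3 U dose and 1 − (1 − q)⁴ for a 4 U dose.

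| q (assumed) | 3 U dose | 4 U dose |
|---|---|---|
| 0 | 0 | 0 |
| 0.05 | 0.007 | 0.185 |
| 0.10 | 0.028 | 0.344 |
| 0.25 | 0.156 | 0.684 |
| 0.50 | 0.500 | 0.938 |
| 1 | 1 | 1 |

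These values show sensitivity to q. They are not predictions for this trial.

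**The case against.** The best defence is that the purpose clause already limits the rule. It speaks of the ABP sum and its constituents, it follows directly on SAP 6.1, and SAP section 4 says that derived data are calculated as 6.1 outlines. On that reading the derivations meant are those of 6.1, of which only ABP and ABPadj count units. This is a reasonable reading and may be the intended one. But the clause gives a reason and not a limit, plasma is itself a constituent of ABP, and nothing sends a programmer back to units as transfused when grading UDPB.

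Several stronger conclusions that a reader might draw are not supported:

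- *That all plasma is doubled and every FP dose becomes severe.* Non-apheresis plasma keeps a factor of 1, and a wholly non-apheresis dose stays class 2. Protocol 1.1 describes FP as coming from whole-blood donation, which points towards that factor, although SAP 6.2 plainly allows for apheresis and unlabelled units.
- *That only the FP arm is touched.* This is true of assigned doses, but not of FP given in the PCC arm from the third order.
- *That a percentage-point excess or a p-value can be attached.* Either would need an assumed share, an assumed underlying rate and an assumed definition of major bleeding. The documents give none of these.
- *That the whole FP–PCC gap on raw UDPB comes from SAP 6.2.* Without conversion, two FP doses are already class 3 against class 2 for two PCC doses.
- *That the per-protocol exclusion "Patients who receive less than 80% of the planned dose" is corrupted.* This would require dividing donor exposures by a planned dose stated in issued units. The plasma factors are also headed as applying to plasma used in transfusions, and membership of the analysis sets is settled at the data review meeting. The reach is speculative.

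It also stands that the planned modified UDPB would help to expose an FP excess present only in the unmodified score, and that S2 is exploratory.

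**Conclusion.** The point holds as a defect of scope in SAP 6.2. Followed as written, the rule gives a wrong UDPB class for patients whose plasma is apheresis or unlabelled. One such unit in a 4 U dose, or two in a 3 U dose, is enough to turn moderate into severe; two fully converted doses turn severe into massive.

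The consequence is limited to the unmodified UDPB and its FP component in S2, and it bears mainly on the FP arm. Its size in this trial is unknown, and would be zero if all plasma were recorded as non-apheresis. The conclusion rests on the literal reading of the timing clause; under the narrower reading no error arises, but the SAP does not say which reading applies. It should be corrected, because the literal reading gives a wrong grade and the remedy is trivial.

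**What to change.** Add to SAP 6.2 a sentence to this effect: the conversions apply only to ABP, ABPadj and their donor-exposure constituents (P2 and S3); UDPB classes and components (S2) use units as transfused. For clarity the same sentence can say that IMP dose summaries (SAP 4.3) and the 80% dose rule (SAP 3.5) also use units as transfused.

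The cost is one sentence in the SAP and a matching line in the programming specification. No new data are needed.

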## 7 REFERENCES

No specific references were used.

|                                  |                        |                    |                      |
|----------------------------------|------------------------|--------------------|----------------------|
| Statistical Analysis Plan | Version 2.0     |                    | Page 19 of 19 |
| Sponsor                   | [name] | Protocol No | FARES         |

## **APPENDICES**

### **1. List of Tables, Listings, Figures**

A complete List of tables, listings, figures (TLFs) will be given in a separate document which can be updated without updating the SAP. The List will serve as a reference for the Sponsor, the TS and the statistical programmer and describes the entire set of statistical output to be produced. Therefore, this List will be versioned and approved by both Ergomed and Sponsor before commencing the statistical programming.

Each output page will have an appropriate heading specifying the study ID and abbreviated study title.

Each output page will show a common date and page numbers in the form 'Page [x / y]' where x denotes the current page within an output and y the total number of pages of that output. The output pages will not contain any other sequential page numbering.

All statistical output will identify the underlying analysis set(s) and indicate the number of subjects/events in this set (N) and the number of subjects/events actually contributing to the particular output (n).

All subject listings will contain in addition to the subject identification the treatment arm and the analysis set.
